### HMI Beta Phase Action Pathway

#### In-Depth Initiative Components

##### Inter-professional Collaboration: Coach Selection and Training

In order to facilitate inter-professional collaboration, which is an integral part of this initiative; coaches from each of the three professions (Physicians, Nurses/Nurse Practitioners, and Pharmacists) at each of the sites were identified to function as enablers and to provide a link between the enrolled sites and the HSFO. The coaches were identified at each of the sites and invited to attend an orientation session for this role. During the course of the HMI, regular communication with the participating healthcare providers will be maintained including periodic meetings of practitioners will continue for the three years of the project.

##### Site Selection and Provider Recruitment

A total of 11 primary care practice sites have been recruited for the HMI Beta Phase. At these sites, there are a total of 49 family physicians and 15 nurse practitioners, each of whom is asked to recruit 100 to 200 patients per full time equivalent rostering physician/nurse practitioner, a potential for up to 8,000 patients. Criteria for site recruitment are found in Table 4.

**Table 4 T4:** Criteria for site recruitment

• Organized primary healthcare team configuration (e.g. Family Health Teams, Family Health Networks, Community Health Centers) that have a capitated or salaried fee structure. (for definition of these types primary care practice groups, see footnote)
• Geographic vicinity to reflect Ontario's diverse needs (northern, urban, and rural).
• Minimize cross research bias. Each primary healthcare team selected will not be participating in any other hypertension studies

Community pharmacists were recruited based on a convenience sample of the community pharmacies neighboring each of the participating medical clinics. To date there have been more than 150 pharmacists recruited. The final breakdown of potential participating healthcare providers by site is provided in Table 5. Each healthcare provider will have access to a variety of tools and resources to assist in improving management of hypertensive patients. There are no risks anticipated from a healthcare providers' participation in this study.

**Table 5 T5:** Recruited HMI Beta Phase Sites

**Pilot Site Community** **(listed by number)**	**Type of** **Primary Care Site**	**Medical** **Record Type**	**# Physicians** **+ NP**	**# NP**	**# Nurses** **(RN and RPN)**	**# Pharmacists**
1	FHT	Paper	16	1	0	21

2	FHT	EMR	1	2	2	6

3	FHT	EMR	5	1	3	25

4	FHT	EMR	10	0		1

5	CHC	Paper	1	4	3	12

6	FHT	EMR	3	1	2	13

7	FHT	EMR	9	1	2	20

8	FHT	Paper	2	1	1	4

9	FHT	Paper	1	2	1	16

10	FHT	Paper	10	1	6	7

11	*FHT*	EMR	5	2	4	7

Total			63	17	25	132

FHT = Family Health Team, CHC = Community Health Centers

A series of tools were developed and piloted in the in the alpha phase of this initiative. These include specific tools for physicians, nurse practitioners and pharmacists as well as tools for patients. Descriptions of these tools are given in Table 6.

**Table 6 T6:** HMI Healthcare Provider and Patient Toolkits

**Toolkit**	**Tool Name**	**Description**	**Target Audience**
**Provider Toolkit**	1. Rx Dx Pads (with Diagnosis check off)	Communication tool for physicians to provide pharmacists diagnosis information with prescription allowing pharmacist to counsel patient appropriately and reinforce physician's messages regarding treatment adherence. It will be available in both paper and electronic form according to site preference.	Physician/Nurse Practitioner

	2. Proper Methods to Take Blood Pressure	A summary of directions for providers and patients on how to take blood pressure; includes step by step instructions for patients before and during BP measurements to ensure a correct BP reading.	

	3. Bp TRu 300	Automated office blood pressure measurement devices.	

	4. Blood Pressure Pocket Guide	An easy to use reference, pocket guide with Blood Pressure Risk chart/BMI calculator, waist circumference risk and stages of Change and counselling information to help your patients with their identified lifestyle modification. Patients also like the visual risk mapping format of the charts.	Provider

	5. HBP Flow Sheet & Assessment Form	Charting tool to record patient's progress with HBP care plan over time. This tool will remain in the patient's chart and will be used in paper version only in paper based sites. That form will be also faxed to an optical recognition site that will digitize the data and send it to a secure web-based custom data set. EMR (electronic medical record) sites will be sending the data directly to the same secure web based custom data set through a secure link.	Provider

	6. Confidential Provider Practice Audit Reports	Regular confidential practice reports are generated from the web-based data set and provided to the healthcare providers, namely physicians and nurse practitioners. The reports provide confidential, anonymous comparisons of one's practice to other participating healthcare providers and sites. The dataset is hosted on a PHIPA compliant server.	Physician/Nurse Practitioner

	7. RNAO-HSFO Nursing Best Practice Guideline, Nursing Management of Hypertension	A nursing best practice guideline collaboratively developed by the Registered Nurses' Association of Ontario and the Heart and Stroke Foundation of Ontario, with funding support from the Ontario Ministry of Health and Long-Term Care. This guideline has been endorsed by CHEP.	Nurses, Nurse Practitioners

	8. CHEP Recommendations	Canadian Recommendations for the Management of Hypertension, published yearly by the Canadian Hypertension Education Program(CHEP)	

	9. 'Reach Your Goal in Your Blood Pressure Control' Fact Sheet	The Reach Your Goal fact sheet is intended as an aid to assist in the lifestyle counselling of hypertensive patients. Patient Lifestyle changes and the effect on Blood pressure are listed on the first side. The other side has Blood Pressure Basics: one page patient education piece on blood pressure that outlines definitions and management. No major changes to the previously ethically approved version except updating information based on the new CHEP guidelines.	Pharmacists

**Patient Toolkit**	1."Take the Pressure Off' Resource Book	Evidence-informed patient HBP education workbook will be provided to all patients. It will serve as a knowledge resource utilizing easy language. This resource will also serve as an identification tool for the pharmacist to initiate lifestyle counselling with the enrolled and consented patients. It is consistent with the latest CHEP recommendations. There are 3 key components of this patient resource book: i) An easy to read resource book designed to provide your patients with a basic understanding of high blood pressure and to promote self-management ii) Patient-Provider Agreement: A tool intended to promote conversations and concordance between patients and you, as well as patient's decision-making. iii) iii) Patient Log Book: An interactive tool that promotes self-management among patients. It enables monitoring of their progress for 3 key co-morbidities: hypertension; diabetes; dyslipidemia, and tracking of medications and questions/topics they wish to follow-up with different members of the healthcare team.	Patient

	4. Blood Pressure Action Plan	HSFO online or phone-in service that asks an individual questions regarding lifestyle and risk factors and offers a personalized plan with realistic strategies for living a healthier life. Individuals may also opt into an email support program that sends periodic email messages to help the individual through the stages of change. Previously ethically approved and no changes has been introduced.	General public patients who enter the Initiative will be referred to BPAP.

The patient will also be offered the patient toolkit, including the "Take the Pressure Off" education/resource book. This patient resource provides information and education on hypertension, its risk factors, lifestyle change information, and lists other resources. The Patient-Provider Agreement is incorporated into the "Take the Pressure Off" book and is to be reviewed and completed during the initial enrolment visit, including the BP goal, the patient's selected lifestyle risk factor which (s)he wishes to focus on in the coming months/years and the patient's personal plan of action for this selected lifestyle risk factor. Documentation of the BP goal and patient selected lifestyle risk factor in the HBP Flow sheet is also done.

Prescriptions are written using an 'Rx Dx' prescription (seen in figure 2), in which any diagnoses of hypertension, dyslipidemia or diabetes can be identified at the bottom of the prescription. This enables the communication of these diagnoses to the patient's pharmacist, who can then support and reinforce the key messages and offer further lifestyle and medications counselling to the patient. A patient counselling tool, the "Reach Your Goal of BP Control" fact sheet, is provided to the pharmacist, for use in patient counselling.

**Figure 2 F2:**
[figure not shown]
**Rx Dx Prescription**.

An office automated blood pressure monitor, the BpTRU, is provided to each family physician and nurse practitioner. The BpTRU monitor is to be used to take the blood pressure reading [6]. As data from each healthcare provider (physicians and nurse practitioners) is inputted in the web based data set, confidential practice audit reports will be produced for each healthcare provider. The HMI's supporting practice and behavior change tools that are to be integrated into practice will be presented during the Launch Workshop.

##### Assignment to Immediate Intervention and Delayed intervention groups

Assignment to the immediate intervention and delayed intervention groups will be conducted at the site level rather than at the practitioner level or patient level. This is to mitigate the potential risk at a site of "contamination" of the comparison by practitioners sharing tools and information about hypertension management (as well as patients), if some practitioners at a site were assigned to the immediate intervention group and some to the delayed intervention group.

Initial consideration was given to randomizing the groups, however with only 11 sites, randomization posed risks of introducing bias. Sites in neighbouring communities could have cross contamination; the diverse and vast geography of the Province of Ontario must be accounted for, particularly because of the more rural north and the more densely populated south. Also, approximately half of the clinics had adopted an electronic medical record at study start, indicating the potential for the more rapid adoption of new techniques. With only 11 sites and too many variables to stratify by to allow randomization, in order to ensure that the sites in the immediate intervention and delayed intervention groups are not different from each other, the sites will be assigned to the intervention groups manually to ensure a distribution of the variables as evenly as possible. Allocation of sites into immediate intervention and delayed intervention groups will also take into consideration geographic proximity between sites. Sites in neighbouring communities will be allocated to the same grouping since communication between participants in proximal groupings could potentially contaminate comparisons.

Demographic and baseline data will be compared between the immediate intervention and delayed intervention groups to determine if the groups did differ significantly in terms of healthcare provider practice patterns, site characteristics, and patient blood pressure control before the implementation of the program. If any statistically significant differences are detected between immediate intervention and delayed intervention groups, then these will be taken into account in analyses following the immediate intervention. The immediate intervention group will have the intervention for a longer duration than the delayed intervention group, providing an opportunity to determine whether there is a "dosage effect" associated with having the immediate intervention for a longer time period.

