**Discussion:**

Initial consideration was given to randomizing the groups, however, for a number of reasons, this was deemed to not be possible. In order to ensure that the sites in the immediate intervention and delayed intervention groups are not different from each other, the sites will be assigned to the intervention groups manually to ensure a distribution of the variables as evenly as possible.

Given that HSFO approached this particular group of health care providers to participate in a program relating to hypertension, this may have heightened their awareness of the issue and affected their management of patients with hypertension. Thus, data will be collected to allow an assessment of previous practice patterns and determine any impact of the Hawthorne Effect.

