## Methods and design

### Overview of the Evaluation Methodology

#### Evaluation Design

To evaluate this initiative, a prospective delayed intervention design has been selected. See Table 2 for key evaluation indicators. Although all sites ultimately will receive the intervention, six of the sites will be assigned to receive the intervention immediately (these sites will be referred to as "immediate intervention group"), while the remaining five sites will receive the intervention after several months, but will serve as a comparison during this delay period (these sites will be referred to as "delayed intervention group"). Further details regarding assignment to the immediate and delayed intervention groups will be discussed in a later section.

**Table 2 T2:** Key Evaluation Indicators of Interest

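### Few sites and many balancing variables rule out stratified randomization, not a random draw among balanced allocations, so the stated case for assigning sites by hand does not hold

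*Protocol article*

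**What the plan says.** Under Evaluation Design, "six of the sites will be assigned to receive the intervention immediately" and "the remaining five sites will receive the intervention after several months". The section on assignment to the two groups says that allocation "will be conducted at the site level rather than at the practitioner level or patient level", to limit contamination. It then says that "with only 11 sites, randomization posed risks of introducing bias" and names the factors to respect: the contrast between the rural north and the populated south, electronic versus paper records, and proximity ("Sites in neighbouring communities will be allocated to the same grouping"). Its reason is given as "With only 11 sites and too many variables to stratify by to allow randomization", and it concludes that "the sites will be assigned to the intervention groups manually to ensure a distribution of the variables as evenly as possible", and gives as the purpose that the two groups should not differ. The Discussion part of the Abstract is shorter: "Initial consideration was given to randomizing the groups, however, for a number of reasons, this was deemed to not be possible".

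The same section plans to compare the groups at baseline and to take account of those differences that reach statistical significance. The Abstract's Methods and the Rationale for the Evaluation Design give the comparison of the two waves at Time 3 the task of separating the program from outside trends.

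**The concern.** The argument goes from too few sites for stratification directly to assignment by hand and leaves out the usual method between the two. Each named factor can be written as a rule that an allocation passes or fails. The acceptable allocations can then be listed and one drawn at random.

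The statement that randomization risks bias is also wrong in kind. With 11 sites the risk is chance imbalance, which the rules limit. Hand assignment balances the listed variables and leaves every other site feature open to the assigner's judgement.

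The Time 3 contrast is at stake. It is the only planned test of the program against concurrent usual care. If some unlisted feature, such as readiness to change practice, influences which sites go first, its effect cannot be separated from that of the program.

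**Working it through.** The plan gives no figure for the number of possible allocations, so there is none to reproduce. The check asks whether enough acceptable splits exist to draw from.

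**Inputs.** From Evaluation Design: 6 immediate and 5 delayed sites. From Table 5: electronic records at sites 2, 3, 4, 6, 7 and 11 (6 sites), paper at sites 1, 5, 8, 9 and 10 (5 sites), and provider counts in the physician column of 16, 1, 5, 10, 1, 3, 9, 2, 1, 10 and 5 (sum 63). Neighbours and north/south location are not given by site, so they are varied as assumptions.

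**Step 1, all splits.** C(11,6) = 462.

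**Step 2, record type.** The most even division is 3 electronic + 3 paper against 3 electronic + 2 paper: C(6,3) × C(5,3) = 20 × 10 = 200.

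**Step 3, neighbours kept together.**
- One pair, worked by hand (both immediate + both delayed). Two electronic sites: C(4,1) × C(5,3) + C(4,3) × C(5,3) = 40 + 40 = 80. Two paper sites: C(6,3) × C(3,1) + C(6,3) × C(3,3) = 60 + 20 = 80. One of each: C(5,2) × C(4,2) + C(5,3) × C(4,3) = 60 + 40 = 100.
- Two separate pairs: all 55 × 36 / 2 = 990 possible choices were enumerated. Between 32 and 52 splits remain, median 40.
- Three separate pairs: 0 to 28 remain, median 20.

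**Step 4, provider numbers as an extra rule.** The assignment section does not name this variable. Added to record-type balance, it leaves the following counts.

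| Immediate group's share of the 63 providers | No neighbour rule | Two pairs tied: median (range) |
|---|---|---|
| 40–60% | 101 | 21 (0–40) |
| 45–60% | 77 | 17 (0–36) |

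**Step 5, region (assumed).** With 3 to 5 northern sites balanced to within about one site, on top of record type and the 40–60% provider band, the median number left is 36, 17 and 8 for one, two and three neighbour pairs. Fewer than two splits remain in 0.1%, 0.9% and 3.3% of simulated patterns. A stricter case (four northern sites split 2/2, two pairs, 45–60% band) has a median of 7 (range 0–27), and 4% of draws leave fewer than two.

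**Step 6, permutation test.** With K equally likely splits the smallest attainable p-value is 1/K, so p = 0.05 needs K of at least 20. With K = 17, 1/17 = 0.059. Under the 45–60% band with two pairs, 74% of the 990 patterns leave fewer than 20 splits. Under record type and two pairs alone none does, since the minimum is 32.

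**Step 7, does the baseline check compensate?** Take a site-level characteristic that differs by one between-site SD, 6 sites against 5. The noncentrality is 1/√(1/6 + 1/5) = 1.65, and a two-sided 5% t test on 9 degrees of freedom has about 31% power. Adjusting only for significant differences would miss such an imbalance about two times in three.

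**The case against.** The strongest reply is that the choice is open and reasoned. The article states that assignment is not randomized and names its criteria, and no passage says that readiness decides who goes first. It also plans safeguards: blood pressure, site characteristics and practice patterns at Time 1 in both groups, a baseline comparison with adjustment, and chart data from before and after first contact. A reader might infer that readier sites were in fact favoured. The documents do not show that; they show only that the method leaves room for it. The safeguards help, but Step 7 shows that a significance filter is a weak one with 11 sites.

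Three other strong readings are tempting and are not supported.
- **That a constrained draw certainly meets every stated rule.** Without neighbours and regions by site this cannot be verified, and a few extreme patterns leave no split at all.
- **That a draw removes selection from the controlled comparison.** It does so for site assignment only. Under Patient Recruitment Strategy and Consent, providers identify patients shortly before their own site's workshop, when the group is known. Time 3 also sets immediate-group patients at follow-up against newly enrolled delayed-group patients at baseline, so patient selection, attrition and regression to the mean remain. Nor is Time 3 the only between-group contrast, since a duration-of-exposure contrast and chart-based comparisons are planned too.
- **That a draw by itself provides a permutation test.** By Step 6 this needs at least 20 splits, which tight provider balance often does not leave.

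On timing, the Abstract's Methods describes enrolment in the past tense while other sections use the future, so sites may already be assigned.

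**Conclusion.** The point holds in limited form. The stated reasons exclude simple or stratified randomization and do not support the conclusion that sites had to be assigned by hand. Constrained randomization was very likely feasible: 200 of 462 splits balance record type, and 32 to 52 (median 40) remain with any two neighbour pairs tied. This rests on the record types in Table 5 and on assumed neighbours; the final count also depends on regions that the article does not list by site. The gain is confined to site assignment. Balancing a few listed variables by hand cannot guarantee that the groups do not differ, and adjusting only for significant differences does not make up for it. This should be corrected; it does not by itself invalidate the design.

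**What to change.** **If sites are not yet assigned:** list the 462 splits, keep those that meet the record-type, north/south and neighbour rules, and draw one at random with a recorded seed. Keep any provider-number balance loose, and check that at least 20 splits remain if a permutation test at 0.05 is wanted. The cost is a short script and one protocol paragraph, with no new sites, patients or visits. The small downside is that the sponsor no longer chooses which sites launch first.

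**If sites are already assigned:** withdraw the statement that manual assignment ensures the groups are not different and describe the Time 3 comparison as non-randomized. Adjust it for the prespecified balancing variables and Time 1 blood pressure control whether or not baseline differences are statistically significant. This is a change of text and model specification; the Time 1 data are already planned.

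In either case, say that provider selection of patients, attrition and the follow-up-versus-baseline contrast at Time 3 need separate handling.

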**Methods:**

This study will test the effect of a systems change on the management of high blood pressure in real world practice in primary care in Ontario, Canada. The systems change intervention involves an interprofessional educational program bringing together physicians, nurses and pharmacists with tools for both providers and patients to facilitate blood pressure management. Each of two waves of subjects were enrolled over a 6 month period with the initial enrollment between waves separated by 9 months. Blood pressure will be measured with the BpTru ^® ^automated blood pressure device. To determine the effectiveness of the intervention, a before and after analysis within all subjects will compare blood pressure at baseline to annual measurements for the three year study. To assess whether the intervention has an impact on blood pressure control independent of community trends, a betwen group comparison of baseline blood pressures in the delayed wave will be made with the immediate wave during the same time period, so that the immediate wave has experienced the intervention for at least 9 months. The total enrollment goal is 5,000 subjects. The practice locations include 10 Family Health Teams (FHTs) and 1 Community Health Centre (CHC) and approximately 49 primary care physicians, 15 nurse practitioners, 37 registered nurses and over 150 community pharmacists across the 11 communities throughout the province of Ontario. The 11 primary care sites will be divided into immediate and delayed groups based on geography and the use of an electronic versus a traditional chart patient record.

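### Adjusting the immediate-versus-delayed comparison for site, practice and pre-programme blood pressure differences depends on a baseline significance test, a poor guide to confounding with 6 versus 5 non-randomised sites

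*Protocol article*

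**What the plan says.** The section on assignment to the two groups states that allocation "will be conducted at the site level rather than at the practitioner level or patient level". Randomisation was considered and rejected; instead "the sites will be assigned to the intervention groups manually to ensure a distribution of the variables as evenly as possible". Under Evaluation Design, "six of the sites will be assigned to receive the intervention immediately" and "the remaining five sites will receive the intervention after several months".

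The assignment section then plans a baseline comparison of the groups on "healthcare provider practice patterns, site characteristics, and patient blood pressure control before the implementation of the program", and gives the rule for using the result: "If any statistically significant differences are detected between immediate intervention and delayed intervention groups, then these will be taken into account in analyses".

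Statistical Design and Analysis names ordinary two-sample t tests and chi-square or Fisher tests, without mention of clustering by site. It also plans regression on covariates known to affect blood pressure. That sentence carries no p-value condition, names no covariate and is not linked to a particular comparison.

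**The concern.** A factor confounds the group comparison to the extent that it is unbalanced and related to blood pressure. A p-value measures neither; for a given imbalance it depends mainly on the number of units tested. The rule screens variables at site, provider and patient level, where that number ranges from 11 to possibly thousands, so the same trigger means very different things for different variables.

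The immediate-versus-delayed comparison at Time 3 is the article's means of separating the intervention from community trends. Without randomisation, that comparison relies on hand-balancing and on adjustment. If adjustment waits for a significant test, a sizeable site-level imbalance can pass unadjusted, and the content of the model depends on the baseline data.

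**Working it through.** **Inputs from the article**
- Sites: 6 immediate, 5 delayed (Evaluation Design).
- Record type: 6 electronic and 5 paper sites, counted from Table 5. The text agrees: "approximately half of the clinics had adopted an electronic medical record at study start".
- Two-sided tests, alpha 0.05, target difference 5 mmHg, 337 per group (Statistical Design and Analysis).
- Enrolment: "The total enrollment goal is 5,000 subjects" (Abstract, Methods).

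**Assumptions (not in the article)**
- SD of blood pressure, back-solved below.
- An equal split, 2,500 per group, with pre-programme readings on all patients. The alternative shown is 337 per group.
- Intracluster correlation (ICC) 0.01 to 0.05.

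**1. The plan's own figure.** n per group = 2 × SD² × (z₀.₉₇₅ + z_power)² / 5². With SD 20 and power 0.9: 2 × 400 × (1.960 + 1.282)² / 25 = 336.2, rounded up to 337. The article gives no SD, so this does not confirm 20. It also states beta = 0.20, which conflicts with power 0.9; at power 0.8, 337 per group implies an SD of about 23.2. Both values are carried forward.

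**2. Site level, continuous characteristic.** The smallest significant difference in group means, in between-site SDs, is t₀.₉₇₅,₉ × √(1/6 + 1/5) = 2.262 × 0.6055 = 1.37. From the noncentral t distribution with 9 degrees of freedom:

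| True imbalance (between-site SDs) | Chance the rule triggers |
|---|---|
| 0.5 | 11% |
| 1.0 | 31% |
| 1.5 | 60% |
| 1.91 | 80% |

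**3. Site level, binary characteristic present at 6 of 11 sites.** There are C(11,6) = 462 possible allocations. The number with a of the 6 in the immediate group is C(6,a) × C(5,6−a): 6, 75, 200, 150, 30 and 1 for a = 1 to 6.

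| Immediate v delayed | Fisher two-sided p | Triggers? |
|---|---|---|
| 6/6 v 0/5 | 1/462 = 0.002 | yes |
| 5/6 v 1/5 | (30 + 6 + 1)/462 = 0.080 | no |
| 4/6 v 2/5 | 0.57 | no |
| 3/6 v 3/5 | 1.00 | no |
| 2/6 v 4/5 | (75 + 30 + 6 + 1)/462 = 0.24 | no |
| 1/6 v 5/5 | (6 + 1)/462 = 0.015 | yes |

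Expected counts lie between 2.3 (5 × 5/11) and 3.3 (6 × 6/11), so the plan's small-cell provision points to Fisher. Pearson's chi-square for 5/6 v 1/5 would be 11 × (5×4 − 1×1)² / (6×5×6×5) = 4.41, p about 0.04. Whether this imbalance counts therefore depends on the choice of test.

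**4. Patient level, clustering ignored.** The smallest significant difference is 1.96 × SD × √(2/n).

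| n per group | SD 20 | SD 23.2 |
|---|---|---|
| 2,500 | 1.1 mmHg | 1.3 mmHg |
| 337 | 3.0 mmHg | 3.5 mmHg |

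For a proportion near 50% with 2,500 per group, it is 1.96 × √(2 × 0.25/2500) = 2.8 percentage points.

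**5. Effect of clustering on that test.** Mean site size is m = 5000/11 = 454.5, and the design effect is 1 + (m − 1) × ICC. This is 5.5 at ICC 0.01 and 23.7 at ICC 0.05. With no systematic group difference, the naive test is significant with probability 2 × [1 − Φ(1.96/√design effect)], which is about 40% and 69%.

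**The case against.** **Other adjustment is planned.** A reader might infer that a significant baseline test is the only route to any adjustment. The article does not say that. It makes significance sufficient, and the planned regression on covariates known to affect blood pressure has no p-value condition. Age, sex or diabetes plausibly enter that way, and leaving the covariate list to a fuller plan is normal for an article. This stands. What remains is that the regression sentence does not clearly cover site characteristics, practice patterns or pre-programme blood pressure control, and does not tie them to the group comparison. For those, the significance rule is the only explicit one.

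**Record type is hand-balanced.** A 5-to-1 split of electronic records is what manual assignment works against, and 3/6 versus 3/5 is available. This also stands: the split illustrates how insensitive the rule is and is not a forecast. Balancing is nevertheless limited, because neighbouring sites must share a group and the article says there are too many variables to stratify by.

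**Flagging small differences does little harm.** Largely true: adjusting for a small blood pressure difference costs almost nothing. The site-level weakness is the more serious half. The patient-level figures mainly show that the trigger does not track importance.

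**The main effectiveness analysis is within subjects.** A reader might infer that the before-after result is also confounded by group imbalance. It is not, because patients and providers serve as their own comparators there.

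**Conclusion.** The concern holds for the between-group comparison. The article states a decision rule that suits a non-randomised comparison of 6 with 5 sites badly. The site-level result (31% power at one between-site SD; Fisher p = 0.08 for 5/6 v 1/5) needs only the site numbers, alpha 0.05 and, for the power figure, roughly normal site means. Power is low but not absent: it reaches 60% at 1.5 SD. The patient-level thresholds of 1.1 to 3.5 mmHg rest on an assumed SD and on sample sizes the article does not give for pre-programme data; the 40% to 69% false-flag rate also rests on an assumed ICC.

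The documents do not show that a severe imbalance will occur, only that one could go unadjusted under this rule. Nor do they describe how intervals will be computed, so a claim that the intervals ignore the selection step would be inference.

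**What to change.** Delete the significance trigger. For the immediate-versus-delayed comparison, prespecify adjustment whatever the baseline p-values for:
- pre-programme (Time 1) blood pressure, which Table 3 schedules in both groups;
- the factors used in assignment, namely record type and a simple geography indicator, with no more than one or two site-level covariates in total;
- patient-level covariates of the kind the planned regression already foresees, such as age, sex and diabetes.

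The analysis should account for clustering by site. Baseline imbalance should be reported by its size, not by tests.

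Two cautions apply to Time 1 blood pressure. It is a sphygmomanometer reading, whereas outcomes use the BpTRU device, so it serves as a covariate and not as an interchangeable baseline. The article also does not say that it will be available for every enrolled patient, so the handling of missing values should be stated.

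The cost is about a paragraph of text and one or two of about 9 site-level degrees of freedom (11 − 2 = 9, leaving 8 or 7). With two covariates the t multiplier rises from 2.262 to 2.365, or about 5%, before any gain from explaining variation between sites.
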